### 2.8. Data Analysis

Interpreting the results of both quantitative and qualitative methodologies will be conducted in accordance with Creswell’s recommendations for mixed-methods research [37]. In brief, the analysis plan for each aim is:

*Aim 1: Barriers/facilitators culturally safe dental care.* A two-stage approach to coding will be used in the thematic analysis of transcripts from the interviews. A primary analytical framework (the first stage) will be structured using the interview guide to create a coding scheme [38], which will group and categorize according to questions asked from the interview script. Developing thematic codes will be the 2nd step, which will more deeply reveal the assumptions, perceptions and conceptual constructs that undergird participants’ perceptions of what constitutes culturally safe dental care.

*Aim 2: Provision of culturally safe dental care.* The assessment of provision of culturally safe dental care will be through the perspective of participants who received the intervention; both children and adults. This will be garnered through qualitative interviews at the follow-up assessments, with the same analytical frameworks utilised as described for the analysis of Aim 1.

*Aim 3: Changes in clinical biomarkers.* Analysis of covariance will be performed to determine differences in the primary, secondary and other outcomes between baseline and 12-month follow-up. Causal inference and sensitivity analyses will be used to emulate a target trial approach [39]. This involves specifying the ‘target trial’ that would have been implemented in ideal circumstances (i.e., the impact of a culturally safe dental intervention on systemic disease biomarkers), then analysing the data in a way that emulates this as closely as possible, accounting for confounding and data missing to follow-up. Target trial emulation is an important step for identifying if an RCT is likely to have found a significant effect.

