## Abstract

Background: Indigenous South Australians carry a disproportionate burden of dental diseases, with approximately 80 percent of Indigenous adults having both periodontal disease and dental caries. The chronic inflammatory nature of many dental conditions means there are widespread systemic impacts, particularly on type 2 diabetes, chronic kidney disease and cardiovascular disease. Evidence suggests there are barriers experienced by Indigenous South Australians in accessing timely and culturally safe dental care. This study aims to: (1) elicit the views of Indigenous South Australians regarding their perspectives of what comprises culturally safe dental care; (2) provide such dental care and; (3) assess any changes in both oral and general health using point-of-care testing following receipt of timely, comprehensive and culturally safe dental care. Methods/Design: This mixed-methods study will involve qualitative interviews and an intervention without randomisation. The qualitative component will comprise seeking perspectives of Indigenous South Australians regarding what culturally safe dental care means for them. For the intervention component, participants will take part in oral epidemiological examinations at baseline and 12-month follow-up (after receipt of dental care), which will include collection of saliva, plaque and calculus, as well as completion of a self-report questionnaire. The primary outcome measures—changes in type 2 diabetes (HbA1c), cardiovascular disease (CRP) and chronic kidney disease (ACR)—will be obtained by blood/urine spot from a finger prick/urine collection at baseline and 12-month follow-up via point-of-care testing. Results: Participant recruitment will commence in July 2022. The first results are expected to be submitted for publication one year after recruitment begins. Discussion: The project will have a number of important outcomes, including increased understanding of what culturally safe dental care means for Indigenous South Australians, the delivery of such care, and empirical evidence of how culturally safe dental care leads to better prognosis for chronic diseases linked with poor oral health. This will be important for health services planning, especially in the Aboriginal Community Controlled Health Organisation sector, where the management of dental diseases in a culturally safe manner for better chronic disease outcomes is currently insufficiently understood, planned and budgeted for.

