### 1.6. What about Confounding?

One of the main difficulties in studying links between periodontitis and systemic disease is that they share some risk factors. Any changes in systemic disease biomarkers will be influenced by a multitude of factors, not just treatment of dental disease. These include medical management, comorbidities, new medications, adherence to medication, health literacy and education. Traditionally, randomised controlled trials (RCTs) have been the only study design to identify cause and effect relationships that account for such confounders. For research questions (such as those from this project) in which conducting RCTs are unethical or impractical, causal inference methods can be used to estimate causal effects from observational data [24]. To estimate the causal effects of dental care on selected biomarkers (HbA1c, CRP and ACR) among Indigenous populations, this research project will adjust for multiple confounders including sociodemographic characteristics (e.g., education, income, health literacy), comorbidities, history of and current medication use, among other factors. We will implement cutting-edge sensitivity analysis methods to investigate the impact of the unmeasured confounders on the causal effect estimate [25]. Sensitivity analysis methods indicate how strong the unmeasured confounders would need to be to explain away the observed causal effect, elucidating whether unmeasured confounding had an impact (if any) on the causal effects estimated [26]. The use of sensitivity analysis to investigate the impact of unmeasured confounding on causal effects estimated from observational data is best practice in epidemiological studies [27] and will be incorporated in this research project.

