### 2.5. Data Collection Techniques

Qualitative, self-report and clinical information will be gathered in this study.

*Qualitative:* At baseline, participants, or carers of child participants, will be asked to take part in one-on-one interviews with study stuff to ascertain views on what culturally safe dental care means. At 12-month follow-up, after receipt of dental care, participants will take part in a follow-up interview to capture participant views on the dental care journey. Interviews will follow a standard prompt guide, will be audio-recorded and professionally transcribed.

*Self-report:* Self-report information pertaining to socio-demographic, oral health and general health factors will be gathered at baseline and 12-month follow-up. Socio-demographic factors will include age, sex, education level, employment, number of people who stayed in house the previous night and car ownership. Oral health factors will include self-rated oral health, oral health-related behaviours and quality of life. General health factors will include behaviours such as smoking and alcohol consumption and general health-related quality of life.

*Clinical:* At baseline, each participant will undergo an oral epidemiological examination and provide saliva, calculus and plaque samples. Adults will also provide blood drops (obtained via finger prick) and urine for point-of-care testing for HbA1c, CRP and ACR. This will be repeated at 12-month follow-up, after receipt of the culturally safe dental intervention.

Oral epidemiological examination: This will include tooth presence, dental caries experience, periodontal destruction, gingivitis and calculus, plaque, oral mucosal lesions and dental trauma.

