### 2.7. Provision of Culturally Safe Dental Care

In 2020, the Australian Health Practitioner Regulation Agency, with whom all dental personnel in Australia need to be registered, stated that ‘*To ensure culturally safe and respectful practice, health practitioners must acknowledge colonisation and systemic racism, social, cultural, behavioural and economic factors which impact individual and community health’*. Key points, which will be utilised in the current study, include genuine engagement of Indigenous Australians in oral health care programs in environments that are culturally acceptable and sensitive. The investigators, through leadership of the study’s Senior Indigenous Research Officer ([name]), will ensure all study activities are conducted in culturally safe ways. All non-Indigenous staff/students will undertake cultural safety training. Culturally safe practise will be reinforced through monthly debriefing sessions, organised by the study’s Senior Indigenous Research Officer to ensure that the many fears of Indigenous clients in accessing dental care (fear of being judged, fear of not being spoken to with respect, fear of child removal) are acknowledged and mitigated in personal and tailored ways. Through all aspects of data collection and dental service provision, Indigenous participants need to feel safe in any encounter with the dental sector; from the receptionist through to the specialist.

The clinical aspects of the oral health intervention will be based on the technique described by Tonetti and colleagues [37], and occur across a series of visits for each participant, based in each ACCHO’s unoccupied dental clinic or public dental clinics by registered oral health professionals who will receive additional training from the dentally qualified study staff, who have extensive expertise in this area. This involves intensive removal of subgingival dental plaque biofilms by scaling, root-planing and removal of teeth that cannot be saved, following administration of local anaesthesia. It will additionally involve the removal of all active dental caries in the dental hard tissues, including replacement of insufficient restorations, and comprehensive prophylactic cleaning with fluoride varnish. Dental care will commence immediately after the baseline visit. At no time will there be any costs incurred for study participants.

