The strengths of the study include it being the first to obtain and link all the information around oral health and general health through a mixed-methods, culturally safe intervention approach in partnership with the Indigenous South Australian community. The focus on engagement, enabling Indigenous community and individual preferences to play a large role in where and how data collection will take place, and how findings will be disseminated builds upon a platform of reciprocal and respectful research processes across almost 20 years [40]. The findings will also provide evidence of the important role Aboriginal Community Controlled Health Organisations play in linking the oral health–general health praxis to increase understanding at the broader community level of how improved oral health contributes to overall improved general health. Our work will support the recommendations of Poirier and colleagues [41], who suggested that Indigenous leadership in oral health has potential to eliminate many of the chronic disease challenges Indigenous communities face, with an example being expansion of the role of Indigenous Health Workers to provide basic oral health screening, prevention and care. The study has strong Aboriginal representation and leadership (half the authors are Aboriginal), with the study recognized as being a contribution to the health and wellbeing of Australia’s first peoples.

The study limitations include the sample frame for dental disease assessment and provision of culturally safe dental care being pragmatic, that is, utilising convenience sampling methodology, which maybe. there is a risk of sampling bias. While the efforts required to obtain a representative sample are recognised as being both expensive and time-consuming [42]. We remain committed to ensuring culturally safe dental care is provided to all study participants, informed by the findings from the qualitative analysis, and to translating study outcomes indicating the impacts on general health biomarkers resulting from a dental intervention for immediate policy translation. The study team will also work closely with dental clinics and be supported by the SA Dental Aboriginal Health Promotion team if client support is required.

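### Aim 3 promises causal effects of dental care, but the only stated contrast is the same people before and after care, so care cannot be separated from time

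*Protocol article*

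**What the plan says.** The abstract describes the study as "qualitative interviews and an intervention without randomisation". Section 2.7 states that "Dental care will commence immediately after the baseline visit", and the Discussion adds: "We remain committed to ensuring culturally safe dental care is provided to all study participants". Adults have the point-of-care tests at baseline, and section 2.5 says of the second round: "This will be repeated at 12-month follow-up, after receipt of the culturally safe dental intervention". No other measurement occasion is given for the primary outcomes (HbA1c, CRP and ACR).

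For Aim 3, section 2.8 specifies an analysis of covariance of outcomes between baseline and 12 months, and then: "Causal inference and sensitivity analyses will be used to emulate a target trial approach". The target trial is described only as the impact of the intervention on the biomarkers. No alternative strategy is named. The same paragraph closes: "Target trial emulation is an important step for identifying if an RCT is likely to have found a significant effect".

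Section 1.6 sets out to estimate causal effects of dental care by adjusting for a list of confounders, and relies on a further analysis: "Sensitivity analysis methods indicate how strong the unmeasured confounders would need to be to explain away the observed causal effect". The abstract forecasts "empirical evidence of how culturally safe dental care leads to better prognosis for chronic diseases linked with poor oral health".

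**The concern.** A target trial compares at least two strategies, and the data must contain people who follow each. Here the stated plan is one strategy for everybody, and the comparison is between two times in the same people. Whatever else happens to all adults over the 12 months enters the estimate with the same sign and weight as the effect of care.

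Section 1.6 itself says that biomarker changes have many causes besides dental treatment, among them new medication and medical management. Section 1.8 and the Discussion add one more: participants receive their test results at once, which may prompt action whether or not dental care has any effect.

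At stake is the study's central claim on its primary outcomes. The Discussion intends the findings for immediate use in policy. A common 12-month shift would be read as the effect of culturally safe dental care, and recruiting more people would only make that misreading more certain.

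**Working it through.** **Inputs.** 1000 adults recruited (section 2.1); 75% retention, 750 adults at 12 months (section 2.6); biomarkers in adults only (section 2.5). Assumed here: two-sided 5% level, normal approximation, and shifts expressed in SDs of the individual change score. The article gives no shift, SD or effect size.

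**The article's own figure.** 1000 × 0.75 = 750, which agrees. The earlier study cited in section 1.7 gives 749/1011 = 74.1%, or about 741 per 1000.

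**Can care be separated from time?** Code care as 0 at baseline and 1 at 12 months for everyone, as the text implies.

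- Model at 12 months (intercept, care, one covariate): care equals the intercept column; rank 2 of 3.
- Model for both occasions (intercept, time, care, one covariate): care equals time; rank 3 of 4.

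No sample size and no added covariate gives care a column of its own unless some people differ in the care they receive. Characteristics that stay fixed, such as education, are the same at both visits and do not explain a mean within-person change. Factors that move with time do.

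**How readily does a shift unrelated to care become a finding?** With n = 750 and no effect of care, a common shift of d SD is significant with probability Φ(d√n − 1.96) + Φ(−d√n − 1.96), where √750 = 27.39.

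| d (assumed) | d√750 | Probability of p < 0.05 |
|---|---|---|
| 0 | 0 | 5% |
| 0.05 | 1.37 | 28% |
| 0.10 | 2.74 | 78% |
| 0.15 | 4.11 | 98% |

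The before-after change detectable with 80% power is (1.96 + 0.84)/27.39 = 0.10 SD.

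**What would an internal comparison cost in precision?** For a comparison group of n₀ among the 750, SE = √(1/n₀ + 1/(750 − n₀)) in SDs of change, and the detectable difference at 80% power is 2.80 × SE.

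| Share in comparison group | n₀ | SE | Detectable difference |
|---|---|---|---|
| 20% | 150 | 0.091 | 0.26 SD |
| 10% | 75 | 0.122 | 0.34 SD |
| 5% | 37.5 | 0.168 | 0.47 SD |

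If the comparison group were adults without periodontal disease, 20% is the most that the abstract's figure allows (about 80% of Indigenous adults have both periodontal disease and caries). That figure describes a population; the share in this convenience sample is unknown. The same table applies to any other group of that size, such as adults who take up little or no care.

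**The case against.** The strongest reply is that uptake will vary. Care is spread over a series of visits (section 2.7), and section 2.8 refers separately to participants who received the intervention. People who complete care could be compared with people who take up little of it, and an unmeasured-confounding analysis would then have something to act on. Section 2.8 calls its account brief, and a full analysis plan may specify the strategies, time zero and weighting.

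This stands in part. A reader might infer that no causal analysis is possible in this study, or that the confounding analysis is meaningless. The documents do not support that: a contrast by uptake could exist in the data. But the article neither names it nor hints at it, and what it does state is a comparison over time. The point is therefore a mismatch between a stated contrast and a stated claim, and not a complaint about omitted detail.

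A reader might also infer that the stated method leaves every rival explanation untouched. That too goes too far. Sections 1.6 and 2.4 list medication, adherence and medical management among the adjustment variables, which addresses part of one threat. Section 2.2 sets no biomarker threshold for entry, so the usual cause of regression to the mean in the whole group is absent. Nothing in the article points to drift of the testing device. Secular change, the effect of returned results and incompletely measured medical change remain.

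Finally, section 2.8 calls emulation a step towards judging what a randomised trial would have found and does not say that it settles the matter. Aim 3 in section 1.9 is worded as ascertaining changes. Both are fair, but they sit beside the causal wording of section 1.6 and the abstract and do not withdraw it.

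**Conclusion.** The concern holds for the plan as written. With care intended for all from baseline and outcomes compared only over time, the whole-cohort estimate is a before-after change. It equals the effect of care only if nothing would have changed without care, an assumption that section 1.6 contradicts. Impracticality of randomisation, argued in the same section, explains the absence of random allocation; it does not supply a comparator.

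The size is conditional. If a common shift of 0.05 to 0.15 SD of change occurred for other reasons, a significant result would follow in about 28% to 98% of trials with no effect of care. The range is illustrative. The inability to separate care from time does not depend on it.

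It may be tempting to rescue the causal claim by making adults without periodontal disease the main comparator. The documents do not support that. Under section 2.7 those adults still receive study care, including caries treatment, cleaning and fluoride varnish. Sections 1.1 and 1.2 link periodontitis to diabetes in both directions and to raised CRP, so parallel trends is doubtful. Their number is unknown.

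**What to change.** In section 2.8, with matching edits elsewhere:

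1. Label the whole-cohort difference between baseline and 12 months as descriptive before-after change.
2. Delete the sentence on what a randomised trial would likely have found. Soften the causal-effect wording in section 1.6 and the better-prognosis wording in the abstract to match.
3. Keep target-trial emulation and the unmeasured-confounding analysis only as a supporting analysis of a named contrast within the data collected, for example care completed against little or no care taken up. State both strategies, set time zero at baseline, say how medication that changes over time is handled, and use weighting. Report it only if enough adults follow each strategy.
4. Optionally add change by baseline periodontal status or severity, labelled exploratory.

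The cost is wording in the article and the analysis plan; no new participants or procedures are needed. The downside is a more modest headline claim and a less precise comparative estimate: 0.26 SD detectable at best for a comparison group of up to 20%, against 0.10 SD for the before-after change.

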## 3. Results

Participant recruitment for this study will commence July 2022. We anticipate the first results to be submitted for publication one year following initial recruitment.

## 4. Discussion

Culturally safe dental interventions for Indigenous Australians to improve systemic disease biomarkers are essential to inform policy translation that might result in dental care provision as a part of chronic disease management in the Aboriginal Community Controlled Health Organisation setting across Australia. Point-of-care testing is an important element of intervention research involving the collection of biodata because it alleviates involvement of third-party laboratory services, means no storage is required, provides participants with immediate results and requires much smaller volumes of blood and urine. Understanding Indigenous Australian perspectives of what culturally safe dental services are will provide valuable knowledge for the creation of culturally safe training programs both in dental teaching institutions and in continuing professional development modules for dental professionals. The project provides a key example of how carefully calibrated, data-driven disease models can integrate with Aboriginal community views and expectations to estimate disease burden, deliver culturally safe dental care and guide policy decisions for more equitable resource distribution that includes dental as part of chronic disease management for Indigenous Australians.

The strengths of the study include it being the first to obtain and link all the information around oral health and general health through a mixed-methods, culturally safe intervention approach in partnership with the Indigenous South Australian community. The focus on engagement, enabling Indigenous community and individual preferences to play a large role in where and how data collection will take place, and how findings will be disseminated builds upon a platform of reciprocal and respectful research processes across almost 20 years [40]. The findings will also provide evidence of the important role Aboriginal Community Controlled Health Organisations play in linking the oral health–general health praxis to increase understanding at the broader community level of how improved oral health contributes to overall improved general health. Our work will support the recommendations of Poirier and colleagues [41], who suggested that Indigenous leadership in oral health has potential to eliminate many of the chronic disease challenges Indigenous communities face, with an example being expansion of the role of Indigenous Health Workers to provide basic oral health screening, prevention and care. The study has strong Aboriginal representation and leadership (half the authors are Aboriginal), with the study recognized as being a contribution to the health and wellbeing of Australia’s first peoples.

The study limitations include the sample frame for dental disease assessment and provision of culturally safe dental care being pragmatic, that is, utilising convenience sampling methodology, which maybe. there is a risk of sampling bias. While the efforts required to obtain a representative sample are recognised as being both expensive and time-consuming [42]. We remain committed to ensuring culturally safe dental care is provided to all study participants, informed by the findings from the qualitative analysis, and to translating study outcomes indicating the impacts on general health biomarkers resulting from a dental intervention for immediate policy translation. The study team will also work closely with dental clinics and be supported by the SA Dental Aboriginal Health Promotion team if client support is required.

Engaging dental clinics at the beginning of the project ensures they are familiar with the study team, the study’s aims and develops close ties/relationships to support the client. Asking questions of the study team eliminates unnecessary concern by the client, e.g., financial queries.

